## Abstract

**Background:**

Sarcomas are rare cancer with a heterogeneous group of tumors. They affect both genders across all age groups and present significant heterogeneity, with more than 70 histological subtypes. Despite tailored treatments, the high metastatic potential of sarcomas remains a major factor in poor patient survival, as metastasis is often the leading cause of death. Currently, metastatic risk assessment relies mainly on histological grading; yet, this method has limitations due to the disease’s heterogeneity. Advances in genomic and transcriptomic research have identified potential molecular signatures, but these approaches lack reproducibility and prognostic reliability. Therefore, new biomarkers are essential for improving risk prediction and therapy adaptation. Recent studies highlight that sarcoma cells secrete extracellular vesicles, particularly small extracellular vesicles (sEVs). These nanovesicles, abundant in bodily fluids such as blood, urine, and saliva, play a crucial role in tumor development, growth, and metastasis. sEVs contain proteins and nucleic acids that mirror tumor characteristics. Given their presence in blood, sEVs offer a promising avenue for noninvasive molecular cancer analysis via liquid biopsy. Preliminary studies in Ewing sarcoma have shown substantial alterations in sEV-derived transcripts, underscoring their potential in tracking disease progression and treatment efficacy.

**Objective:**

This study aims to investigate whether sEVs can serve as reliable biomarkers for monitoring sarcoma progression and predicting recurrence risk.

**Methods:**

This prospective, multicentric pilot study will enroll adult patients diagnosed with localized or metastatic liposarcomas, leiomyosarcomas, or undifferentiated pleomorphic sarcomas at 3 French cancer centers. The study’s primary goal is to quantify sEVs and analyze their protein and RNA content in the blood of patients with localized or metastatic sarcomas before and after the treatment. sEVs will be isolated from plasma samples, and protein and microRNA concentration will be determined. Research will last, on average, 6 months for patients with localized sarcoma and 4 months for patients with metastatic sarcoma.

**Results:**

We expect to identify differences in exosome levels based on disease stage and observe correlations between exosome dynamics and treatment response. If confirmed, these findings could establish sEVs as noninvasive biomarkers for monitoring therapy effectiveness and disease progression in patients with sarcoma.

**Conclusions:**

This study could establish a novel, noninvasive biomarker for sarcoma prognosis and treatment monitoring. If successful, a nationwide study will be launched to confirm findings in a larger patient cohort, potentially revolutionizing sarcoma management and improving patient outcomes.

**Trial Registration:**

ClinicalTrials.gov NCT03800121; https://clinicaltrials.gov/ct2/show/study/NCT03800121

**International Registered Report Identifier (IRRID):**

DERR1-10.2196/63718

## Introduction

Sarcomas are rare cancers representing 1%-2% of all adult cancers with more than 5000 cases per year in France recently [1]. They affect men and women of all ages and constitute a heterogeneous group of tumors, with more than 70 different histological types and subtypes [2]. Despite adapted therapies, the metastatic risk of these diseases currently has a major negative impact on patient survival. Metastatic dissemination of tumor cells is responsible in most cases for patient death. The estimation of sarcoma’s metastatic risk is complex, given the histological heterogeneity of this pathology. It is therefore essential that, at diagnosis, a reliable evaluation of metastatic potential may be determined to better adapt the therapeutic strategy. Currently, the estimation of this risk is based essentially on histological criteria, namely the tumor grade. In recent years, large-scale genome and transcriptome analyses have allowed the identification of tumor molecular signatures predictive of prognosis. However, results reproducibility can be discussed, and the biological and prognostic significance remains limited. It is therefore necessary to find new biomarkers.

It has recently been found that sarcoma tumor cells secrete extracellular vesicles (EVs) [3] including small EVs (sEVs). In this study protocol, we will use the term exosomes to refer to small EVs. Exosomes are nanovesicles secreted by all the cells of the human body and found in abundance in different biological fluids such as blood, urine, saliva, and breast milk. Recently, the role and involvement of exosomes in sarcoma [4,5] development have been demonstrated [6]. Indeed, exosomes seem to play an important role in tumorigenesis, growth, tumor progression, and metastases appearance. Exosomes contain many proteins and nucleic acids (DNA, RNA, and microRNA), reflecting tumor characteristics. It has been shown that the amount of exosomes can be correlated with the grade of tumor malignancy [7,8]. Present in the blood, they offer the possibility of a noninvasive analysis of cancer cell molecular information by liquid biopsy. Recent preclinical studies have demonstrated strong changes in more than 1200 transcripts present in exosomes derived from Ewing sarcoma cells. Therefore, the study of plasma-derived exosomes in patients with sarcoma has a high potential to evaluate cancer pathogenesis, progression, and treatment efficacy.

The aim of this study is to demonstrate the potential of exosomes as biomarkers for monitoring disease progression and predicting treatment response in patients with both metastatic and nonmetastatic sarcoma.

## Methods

### Study Population

Adult patients with a diagnosed sarcoma, such as liposarcomas, leiomyosarcomas, or undifferentiated pleomorphic sarcoma (UPS) and managed at Georges-François Leclerc Center in Dijon or at Jean Minjoz Center in Besançon or CHU Poitiers.

### Study Objectives and Endpoints

The main objective of this pilot study is to quantify exosomes from plasma and to analyze protein and RNA content in patients with sarcoma, with localized or metastatic disease. Analysis will be performed before and after surgery in localized disease and before and after first-line chemotherapy in metastatic sarcoma. Some patients may have received neoadjuvant chemotherapy with or without radiotherapy.

The secondary objectives are to:

Determine whether the initial exosome concentration, protein, and RNA profile vary in the plasma with localized or metastatic stage of the disease.Determine whether the exosome concentration as well as protein and RNA profile varies upon treatment.Determine whether the initial exosome concentration (T0) is associated with a response to treatment.Determine whether changes in exosome concentration before and after treatment are associated with a response to treatment.

The primary endpoint of the study is the quantification of exosome concentration in the blood, as well as the measurement of protein and RNA levels after exosome lysis. Measures will be performed before and after surgery in case of localized disease and before and after chemotherapy in case of metastatic disease.

The secondary endpoints will be exosome blood concentration, as well as protein and RNA concentrations measured after exosome lysis. Treatment response and tumor progression (locoregional or appearance of metastases) will be assessed by magnetic resonance imaging (MRI) or computed tomography (CT) scan using RECIST (Response Evaluation Criteria in Solid Tumors) V1.1 criteria.

### Study Design

Pilot, prospective, multicentric, nonrandomized study, without direct individual benefit. The study is supported by the Institut National du Cancer (INCa) platform CLIP² (Certified Early-Phase Clinical Trial Centers) at the Georges-François Leclerc Center in Dijon, CHU Poitiers, and Jean Minjoz Center in Besançon. The study inclusion period will be 48 months and the total study duration will be 60 months. Study design is depicted in Figure 1. Research will last an average of 6 months for patients with localized sarcoma and 4 months for patients with metastatic sarcoma.

Investigators receive an informative notice on the EXOSARC (Study of Exosomes in Monitoring Patients With Sarcoma) study and will be provided samples of eligible patients. Upon written patient consent, serology to HIV, hepatitis C virus, and hepatitis B virus will be tested (Figure 1). Only patients with negative serology for these infectious agents will be included, to protect technicians from biological risks, in agreement with laboratory procedures. Exact inclusion and exclusion criteria are available in Textbox 1.

**Figure 1 figure1:**
[figure not shown]
Study design. EDTA: ethylenediaminetetraacetic acid; EV: extracellular vesicle; HBV: hepatitis B virus; HCV: hepatitis C virus.

EXOSARC (Study of Exosomes in Monitoring Patients With Sarcoma) inclusion and exclusion criteria.
**Inclusion criteria**
Men and women diagnosed with localized or metastatic soft tissue sarcoma (liposarcoma, leiomyosarcomas, or undifferentiated pleomorphic sarcomas [UPS]).Adult patients (≥18 years old) with histologically confirmed sarcoma, including but not limited to liposarcomas, leiomyosarcomas, and UPS.Previous treatment of the disease with chemotherapy, radiotherapy, or surgery is allowed if it has been completed for more than 12 months at the time of inclusion.Age ≥18 years old.For metastatic or locally advanced (inoperable) sarcoma, patients for whom first-line metastatic chemotherapy is indicated.Affiliated to French social security or beneficiary of such a regimen.Written informed consent.
**Exclusion criteria**
Patient with other synchronous tumorsPatient with sarcoma in irradiated tissue.Patient with a history of cancer other than sarcoma in the 5 years preceding sarcoma diagnosis.Patient unable to undergo medical follow-up for geographical, social or psychological reasons,Person benefiting from an adult protection system (including guardianship and trusteeship).Positive serology to HIV or hepatitis B virus or hepatitis C virus.Pregnant or lactating woman.Patients unable to understand, read, or sign an informed consent.

### Patient Identification and Recruitment

Patients will be identified and recruited from participating oncology centers through:

Diagnosis codes (*ICD-10* [*International Statistical Classification of Diseases and Related Health Problems 10th Revision*]) and pathology reports from hospital databases.Referral by treating oncologists and multidisciplinary sarcoma teams based on eligibility criteria.Screening during routine clinical visits for patients with newly diagnosed sarcoma or those scheduled for treatment.

### Sampling

A total of 32 mL of blood (8× 4 mL EDTA [ethylenediaminetetraacetic acid] tubes) will be collected at each sampling for exosome analysis in both cohorts.

For cohort 1 (patients with localized sarcoma and undoing neoadjuvant chemotherapy), blood samples will be collected before surgery at cure 1 (sample 1) and at the last cure preceding surgery (sample 2). Then, at 1 month (sample 3) and 6-8 months post surgery (sample 4).For cohort 2 (patients with metastatic or locally advanced inoperable sarcoma), a blood sample will be collected before initial chemotherapy administration (sample 1). Then, at the third (sample 2) and at the sixth chemotherapy treatment (sample 3).Note that sample collection will take place before chemotherapy treatment even if the cure schedule is changed or postponed. Samples will be kept for a maximum of 2 hours at 4 °C.

### Blood Collection and Storage

Plasma will be collected by centrifugation of blood samples (EDTA tube; 2200 rpm for 15 minutes at 4 °C). All the 3 components obtained will be aliquoted and stored on site at −80 °C.

### Extracellular Vesicle Analysis

Thawed plasma samples will be processed to centrifugation at 2000 g at 4 °C for 20 minutes. Exosomes will be extracted with Total sEV Precipitation Reagent (4484450, Thermo Fisher Scientific) for 10 minutes following homogenization. Part of the EVs will be used to determine their concentration and distribution profile using Nanotracking Analysis (NS300, Malvern). The data will be analyzed using Nanosight NTA 3.2 Analytical Software (Malvern Instruments). The other part will be used for the analysis of EV contents (proteins and RNA) and stored at –80 °C. Content analysis (proteins and RNA) will be performed using Western blot analysis, enzyme-linked immunosorbent assay, and RNA sequencing (Illumina) approaches. It is expected that all collected blood will be used for extracellular vesicles and content analysis.

### Data Collection

The following data will be collected during the study, at the time of inclusion, and during medical follow-up: demographic and clinical data (age, sex, weight, height, performance status, etc), medical history, date of diagnosis, first-line treatment, disease evaluation reports (biological, imaging, etc), exosome analysis data (total exosome concentration, HSP70 exosome concentration, and multiple miRNA dosing). These data will be sent as a standard report from the laboratory in charge of these analyses (Inserm UMR1231). All data will be recorded in a Case Report Form (CRF).

### Sample Size

A total of 30 patients, for whom all samples required for the study have been collected, should be included, distributed as follows:

Group 1: 15 patients with localized disease, for whom the 4 samples required for the study were collected.Group 2: 15 patients with metastatic disease, for whom the 3 samples required for the study were collected.

These numbers will provide preliminary data before considering a larger study. The primary objective of this study is to measure the markers of interest in patients. Given that the study focuses on rare cancers and that statistical analyses are only secondary objectives, no statistical power calculation has been performed for this study. Patients for whom the total number of required samples was not achieved will be replaced.

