### Statistical Analysis

Plasma exosomes as well as exosomal protein and RNA concentrations will be described by their mean (SD) and their median (with extent). Comparison of baseline concentrations of participants with localized disease versus metastatic disease will be performed using nonparametric Wilcoxon tests. Comparison of pretreatment and posttreatment (surgical or drug) concentrations will be performed using nonparametric tests for matched data. Analyses will be carried out by subgroup (metastatic and localized) and on the whole population. Relative exosome variation before and after treatment will be compared in responders and nonresponders using nonparametric Wilcoxon tests. A Bonferroni correction will be applied to the *P* value to adjust the significance threshold during multiple comparisons.

The area under the receiver operating characteristic curve (AUC) modeling the response to treatment in function of initial exosome concentration will be plotted. AUCs with 95% CI values will be provided. The model will be adjusted to the type of disease (localized or metastatic). An exosome concentration threshold, predictive of response to treatment, will be determined. Performance (ie, sensitivity, specificity, and predictive values) associated with this threshold will be calculated. A similar approach will be followed concerning exosome concentration after treatment and delta between initial and posttreatment values. Different protein and RNA-derived markers will be analyzed. Performance associated to the absence or presence of these markers to predict response to treatment will be determined for each of the markers. Analyses will be performed under the software SAS 9.4 (SAS Institute).

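### Replacing every patient without a full sample set makes entry to the response analyses depend partly on outcome, mainly in the metastatic group

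*Protocol article*

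**What the plan says.** **Who counts.** Sample Size sets the target: "A total of 30 patients, for whom all samples required for the study have been collected, should be included". The split is "Group 1: 15 patients with localized disease, for whom the 4 samples required for the study were collected" and "Group 2: 15 patients with metastatic disease, for whom the 3 samples required for the study were collected". Then comes the replacement rule: "Patients for whom the total number of required samples was not achieved will be replaced". It makes no distinction by reason.

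**When the last sample falls.** Under Sampling, metastatic or inoperable patients give sample 1 before chemotherapy starts. The schedule continues: "Then, at the third (sample 2) and at the sixth chemotherapy treatment (sample 3"). For localized patients, after two samples before surgery, it reads: "Then, at 1 month (sample 3) and 6-8 months post surgery (sample 4"). Delay is provided for: "Note that sample collection will take place before chemotherapy treatment even if the cure schedule is changed or postponed". Chemotherapy that ends before the sixth treatment is not mentioned.

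**What is analysed.** Statistical Analysis compares baseline concentrations between stages. It also fits a response ROC curve on initial concentration, with a threshold, sensitivity, specificity and predictive values. For change it states: "Relative exosome variation before and after treatment will be compared in responders and nonresponders using nonparametric Wilcoxon tests". Analyses are by stage and overall. The section does not say whether replaced patients belong to the overall population.

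**What is expected.** The Results section anticipates that a higher baseline concentration may go with more aggressive disease.

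**The concern.** In Group 2, having a complete series means having stayed on first-line chemotherapy to the sixth treatment. Patients who progress and stop, or who die, before then are clear treatment failures, and they are the ones replaced. Their baseline blood has already been drawn.

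Two of the planned analyses do not need the later samples. The stage comparison uses sample 1 only, and the baseline ROC analysis uses sample 1 and the response. For these, requiring a full series gains nothing and removes informative nonresponders.

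The stake is what is carried forward. The article presents this pilot as the basis for a nationwide study. A response rate, AUC, threshold and predictive values estimated in completers would describe patients who can be identified only after most of the treatment has been given. They would not describe the patients in whom a baseline marker would be used.

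**Working it through.** **The plan's own figure.** 15 + 15 = 30 complete series, as stated. There is no power calculation to reproduce, and no dropout or response rate is given. All rates below are assumptions.

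**1. Number replaced in Group 2.** If a share q is lost before the last sample, obtaining 15 completers needs 15/(1 − q) patients, rounded up.

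| q | Enrolled | Replaced |
|---|---|---|
| 10% | 17 | 2 |
| 20% | 19 | 4 |
| 30% | 22 | 7 |
| 40% | 25 | 10 |
| 50% | 30 | 15 |

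**2. Apparent response rate.** If all those lost are nonresponders and the true response rate is R, completers show R/(1 − q).
- R = 20%, q = 40%: 0.20/0.60 = 33%.
- R = 20%, q = 20% to 50%: 25% to 40%.
- R = 30%, q = 20% to 50%: 37.5% to 60%.

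**3. Predictive values.** Hold sensitivity and specificity at 0.70 (assumed) and let the response rate move from 20% to 33%.
- PPV = 0.7R/(0.7R + 0.3(1 − R)): from 0.14/0.38 = 0.37 to 0.54.
- NPV = 0.7(1 − R)/(0.7(1 − R) + 0.3R): from 0.56/0.62 = 0.90 to 0.82.

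With R = 30% and q = 20% to 50%, PPV goes from 0.50 to between 0.58 and 0.78, and NPV from 0.84 to between 0.80 and 0.61.

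**4. Baseline AUC, simple model.** Assume 20% respond, 40% are stable and 40% progress early. Take the log marker as normal with SD 1 and means 0, 0.5 and 1.0 in these three classes.
- Responders versus stable: Φ(0.5/√2) = 0.638.
- Responders versus early progression: Φ(1/√2) = 0.760.
- All patients: (0.4 × 0.638 + 0.4 × 0.760)/0.8 = 0.699.
- Completers, with early progressors removed: 0.638.

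With 30% or 50% early loss and response kept at 20%, the all-patient AUC is 0.68 or 0.71. The completer value stays at 0.64.

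**5. Baseline AUC and stage comparison, second model.** One latent outcome axis has correlation rho with the baseline marker. The best 25% are responders and the worst q are removed (large-sample simulation).

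| rho | AUC, all | AUC, completers (q = 20, 30, 40%) | Shift of metastatic baseline mean (SD) |
|---|---|---|---|
| 0 | 0.50 | 0.50, 0.50, 0.50 | none |
| 0.3 | 0.64 | 0.62, 0.60, 0.59 | −0.10, −0.15, −0.19 |
| 0.5 | 0.74 | 0.70, 0.68, 0.67 | −0.17, −0.25, −0.32 |

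Both models give the same direction: if the marker is prognostic, selection attenuates the AUC and lowers the metastatic baseline. If it is not, neither moves, but the response rate and hence the predictive values still do.

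**The case against.** **Exclusion is inferred, not stated.** The article says incomplete patients are replaced; it does not say that their data are discarded. Extracellular Vesicle Analysis expects all collected blood to be used, which fits assaying a replaced patient's first sample. The full protocol or SAP, not shown, may define an analysis set that keeps them. This stands as a limit on certainty. But the 30 are defined by complete series, the replacement rule is fixed in this text, and nothing in it says that replaced patients are kept. The plain reading is completers only.

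**Complete series have a purpose.** The primary aim is to measure the markers over time, and replacement serves that. This is fair, and the remedy keeps the target of 15 complete series per group.

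**The shift is small against the noise.** With 5 responders and 10 nonresponders, the Hanley-McNeil standard error of an AUC of 0.64 is about 0.15 to 0.16, so a shift of 0.06 is about 0.4 standard errors. The attenuation also runs against the marker, so it would not create a false claim of discrimination. This stands, and it lowers the severity.

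**Stronger readings the documents do not support.**
- A reader might infer that both groups are equally affected. In Group 1, sample 4 is a blood draw 6 to 8 months after surgery, and relapse alone does not prevent it.
- A reader might infer that nonresponders in Group 2 would be almost only stable disease. Patients who progress but reach the sixth treatment stay in, and some losses will be unrelated to outcome. The selection is partial.
- A reader might infer that all predictive values are inflated. PPV rises and NPV falls.
- A reader might infer that every secondary objective is biased. The stage comparison is distorted only if baseline concentration is related to early failure. A patient with no later sample cannot contribute a before-after difference under any analysis set.

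**Conclusion.** The concern holds in a limited form. Read together, the Sample Size and Sampling sections make being counted in Group 2 depend on reaching the sixth chemotherapy treatment, and Statistical Analysis then studies response. In Group 1 outcome-related loss can arise only through death, withdrawal or surgery not done.

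Under an assumed 20% response and 40% early loss of nonresponders, 10 of 25 enrolled metastatic patients would be replaced and the response rate would read 33% instead of 20%. At fixed sensitivity and specificity of 0.70, PPV would move from 0.37 to 0.54 and NPV from 0.90 to 0.82. The fall in baseline AUC, 0.70 to 0.64 under the assumed means, and the shift in the metastatic baseline also need a link between marker and prognosis. The article expects such a link but has not shown it.

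The actual size cannot be fixed from the documents, and the conclusion rests on reading replacement as removal from analysis. Because this is a small pilot with a descriptive primary aim and no power calculation, the point should be fixed but does not undermine the primary endpoint.

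**What to change.** Keep the recruitment target and separate it from the analysis set:

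- Continue recruiting until 15 complete series per group exist.
- State that replaced patients with a valid baseline sample stay in the baseline-versus-stage and baseline-versus-response analyses.
- For analysis, count progression or death before the last planned sample as nonresponse, and record response for replaced patients.
- Use all available samples for the change analyses, for example with a mixed model on log concentration, so that a metastatic patient with samples 1 and 2 still contributes.
- Report the complete-series analysis as a sensitivity analysis, with the number replaced in each group and the reasons.

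The cost is wording in the protocol and SAP and the assay of some samples already drawn. Treatment and the sampling schedule are unchanged. The reported response rate will look less favourable. The change should be made before analysis: if replaced patients' samples are not assayed or their response is not recorded, the selection cannot be repaired later.
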